### 2.5. Groups and Randomization

Randomization of participants will be conducted using SPSS 22 statistical software to ensure balanced distribution between gender and BMI categories (overweight and class 1 obesity). Participants will be randomly assigned to the three study groups, and the allocation will be coded to maintain group balance.

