## 4. Detailed Procedure

### 4.1. Sample Size Calculation

To carry out the present study, 156 young sedentary adults with overweight/obesity will be recruited through a snowball sampling. Considering the body composition changes as the primary outcome, the minimum sample size calculated for the present protocol was 44 participants to reliably detect an effect size of δ ≥ 0.5, assuming a two-sided criterion for detection that allows a maximum Type I error rate of α = 0.05 with a probability of 0.9, and considering a 20% dropout of participants, the sample size has been fixed to 52 participants per group. The statistical software used to determine the sample size was G*Power (v3.1.9.7, Universität Kiel, Düsseldorf, Germany) [15]. 

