#### 4.5.4. Dietary and Psychological Counseling

For internal control, covariates that could influence the findings (uncontrollable variables) will be monitored, including dietary patterns, mental health, and adherence of the individuals during the trial period. The food intake of all participants will be monitored through a 24 h quantitative recall of typical days (typical days before the start and at the end of the intervention), as well as a food frequency questionnaire. Food scales will be used to increase precision in food portions. Diet records will be analyzed for total calories, protein, carbohydrate, and fat intake (Diet Analysis Plus, ESHA Research, Salem, OR, USA). Dietary control will be complemented with biomarkers of nutrient intake such as urinary nitrogen and blood concentrations of cholesterol, triglycerides, and glucose.

The psychological status of the individuals will be evaluated using the validated instrument “Depression, Anxiety, and Stress Scale-21” (DASS-21), complemented by sleep-wake patterns obtained through a sleep diary and sleep quality assessment questionnaires (Pittsburgh Sleep Quality Index and Insomnia Severity Index).

Only individuals who complete at least 80% of all training sessions and measurements outlined in this intervention will be included in the data to ensure adherence to the treatments and the validity of the findings. Additionally, electronic and personal contact via text messaging will always be enabled for study follow-up.

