#### 4.5.5. Data Analysis

The normality and homoscedasticity of the variables will be assessed using the Kolmogorov–Smirnov and Levene tests for each group. A student’s *t*-test will be used to analyze the differences between the pre- and post-treatment values for each variable if the data follows a normal distribution. If the data are non-parametric, the Mann–Whitney U test will be used. Statistical analysis between treatments will be conducted using ANOVA with Tukey’s post-hoc test in the case of parametric distribution and/or Kruskal–Wallis H and Dunn’s Post-hoc test for non-parametric distribution, with a Bonferroni setting for comparing intervention-induced changes. Additionally, Pearson and/or Spearman correlation tests will be used to establish associations between variables. Multivariate linear regression models will also be constructed to explore the contribution of treatment on main outcomes, which will be adjusted by potential confounder factors including age, sex, dietary variables, psychological variables, and baseline measurements. Moreover, multiple imputations will be used for generating replacement values for missing data. Statistical significance will be considered at *p* < 0.05, and all statistical analyses will be conducted using IBM SPSS package version 22 (SPSS Inc., IBM Company, Chicago, IL, USA) and GraphPad Prism v8.1 (GraphPad Software, La Jolla, CA, USA).

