If these issues are not properly addressed, the consequences will have serious public health concerns. The prevalence of obesity will continue to rise, increasing the number of people at risk of developing chronic diseases, reducing their life expectancy, and quality of life. In addition, the health care system will face increased costs and pressure, making this silent pandemic even more difficult to manage.

As limitations of this study protocol, we cannot include a double or triple blind randomized trial, due the interventions are related to a FatMax and/or resistance training program and only the data analysis researcher will be blinded. Additionally, it is acknowledged that in addition to exercise, other lifestyle factors might influence microRNA expression, such as diet, sleep quality, emotional stress, or psychological variables, so we will include them in the correlation tests and multivariate linear regression model analysis.

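### The between-arm ANOVA on changes is valid but omits baseline, sex and BMI category as covariates, and the exploratory model does not confine diet and psychological covariates to pre-randomisation values

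*Protocol article*

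**What the plan says.** **Between-arm test.** Section 4.5.5 compares treatments by ANOVA with Tukey's test, or by Kruskal-Wallis with Dunn's test, "with a Bonferroni setting for comparing intervention-induced changes". No covariate or stratum term is named. Section 4.1 likewise defines the primary outcome as changes in body composition.

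**Assignment.** Section 2.5 says that randomisation is meant "to ensure balanced distribution between gender and BMI categories (overweight and class 1 obesity"). Section 4.2 repeats this and gives BMI limits for the two categories.

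**Adjusted model.** Section 4.5.5 adds regression models to explore what treatment contributes to the main outcomes. They are "adjusted by potential confounder factors including age, sex, dietary variables, psychological variables, and baseline measurements".

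**When the covariates are measured.** Section 4.5.4 says that covariates which could influence the findings "will be monitored, including dietary patterns, mental health, and adherence of the individuals during the trial period". It places the diet recall both before the start and at the end of the intervention, and gives no timing for the psychological and sleep scales. Section 2.7 has diet followed regularly through the study and also monitors sleep quality and psychological status. Section 5 notes that diet, sleep, stress and psychological factors may affect microRNA expression, "so we will include them in the correlation tests and multivariate linear regression model analysis".

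**Within-arm tests.** Section 4.5.5 also tests pre against post values for each variable.

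**The concern.** There are two separate issues.

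1. Sex and BMI category are used to balance assignment, and the outcome is measured at baseline, yet none of these enters the between-arm test as a covariate. Subtracting baseline is not the same as adjusting for it, and it is less efficient whenever the pre-post correlation is below 1. A balancing factor that predicts change leaves the standard error too large if it is omitted.

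2. The adjusted model calls diet and psychological variables confounders. Randomised assignment cannot be confounded by something that arises after it. Exercise may itself alter intake, mood, stress or sleep. A value measured on trial may then lie on the path from treatment to outcome, and conditioning on it changes the quantity estimated. Nothing in the article confines these covariates to their baseline values.

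The stake is avoidable imprecision in the main comparison, and an adjusted estimate whose meaning depends on an unstated choice.

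**Working it through.** **Inputs from Section 4.1.** "the minimum sample size calculated for the present protocol was 44 participants to reliably detect an effect size of δ ≥ 0.5"; two-sided α = 0.05; power 0.90; 20% dropout; 52 per group. The article gives no standard deviation and no pre-post correlation ρ, so ρ is taken over a range.

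**Step 1: the plan's own figure.** For a paired t-test with standardised change 0.5 and n = 44, the noncentrality is 0.5 × √44 = 3.317 on 43 degrees of freedom, and the power is 0.900. So 44 reproduces as a within-group pre-post calculation, and 44 × 1.2 = 52.8 was rounded down to 52. Whether that is the right basis for the sample size is a separate question. It matters here only because the between-arm contrast has less power to spare. With a difference of 0.5 change-score SDs, 44 per arm and pairwise α = 0.05, the noncentrality is 0.5 × √(44/2) = 2.345 on 86 degrees of freedom, and the power is 0.64. At α = 0.05/3 it is 0.47.

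**Step 2: change score against baseline adjustment.** With equal variance σ² at both times:
- change-score variance = 2σ²(1 − ρ)
- residual variance after adjusting for baseline = σ²(1 − ρ²)
- ratio = (1 − ρ²) / [2(1 − ρ)] = (1 + ρ)/2

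A difference of 0.5 change-score SDs becomes 0.5 × √[2/(1 + ρ)] residual SDs.

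| ρ (assumed) | Variance ratio | Reduction | Effect in residual SDs | Pairwise power, 44 per arm, α = 0.05 |
|---|---|---|---|---|
| 0.9 | 0.95 | 5% | 0.513 | 0.66 |
| 0.8 | 0.90 | 10% | 0.527 | 0.69 |
| 0.7 | 0.85 | 15% | 0.542 | 0.71 |
| 0.5 | 0.75 | 25% | 0.577 | 0.76 |

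The comparator in every row is 0.64. Any further gain from sex and BMI category cannot be sized from the article.

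**Step 3: an on-trial covariate.** Let treatment shift the covariate by a, and let the covariate have slope b on the outcome. Adjusting for it takes a × b out of the treatment coefficient. With an assumed total effect of 0.5:
- a = 0: nothing is removed
- a = b = 0.2: 0.04/0.5 = 8%
- a = 0.2, b = 0.4: 0.08/0.5 = 16%
- a = b = 0.4: 0.16/0.5 = 32%

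A simulation with 200,000 subjects gave coefficients of 0.46, 0.42 and 0.34 in the last three cases. With the baseline value of the same covariate in place of the on-trial value, the coefficient stayed at 0.50. The values of a and b are illustrative. If a × b is negative, adjustment raises the coefficient instead.

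**Step 4: which values would enter?** Sections 2.7 and 4.5.4 describe on-trial monitoring, and Section 5 treats these factors as influences acting alongside exercise. Against that, diet is also recalled before the start, and Section 4.5.5 names no time point. The text allows either reading. Section 4.5.4 also counts blood cholesterol, triglycerides and glucose among its dietary biomarkers, while Section 2.4 lists glucose and cholesterol as dependent variables. If these were entered as dietary variables at week 16, the model would condition on trial outcomes.

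**The case against.** Several stronger readings are tempting, and the article does not support them.

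- **That the between-arm test ignores baseline.** It does not. Changes use baseline by subtraction, and a comparison of changes is unbiased under randomisation. Leaving out balancing factors errs on the conservative side. What remains is an efficiency argument, and a modest one if ρ is high.
- **That the adjusted model removes part of the effect.** This needs on-trial values in the model and a treatment effect on those values. The article states neither. Listing diet and psychological variables apart from baseline measurements does not settle the timing, since age and sex are listed apart too. The note to Figure 1 puts all participants on an isoenergetic diet, which would limit the dietary path, although Section 2.7 mentions that diet for the control group only.
- **That BMI is excluded from the regression.** The covariate list is open-ended, and its baseline measurements could cover BMI. The category is simply not named.
- **That treatment effects will be read from the within-arm tests.** Section 4.5.5 gives the comparison between treatments to ANOVA or Kruskal-Wallis. Within-arm significance would still be a poor guide. If all three arms truly changed by the protocol's 0.5, each would be significant with probability 0.90 at n = 44, and they would disagree with probability 1 − 0.9³ − 0.1³ = 0.27. That supports descriptive reporting, but it does not show that the plan makes the error.

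The regression is also exploratory and already contains sex and baseline measurements. The timing of exploratory covariates might be settled in a fuller document. These objections narrow the point. They do not remove the missing covariates from the stated between-arm test, or the lack of any restriction on the covariates that the article chose to list.

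**Conclusion.** The point holds as a no-cost improvement and does not threaten the validity of the randomised comparison. The between-arm analysis of changes gives up 5%, 10% or 15% of variance at ρ of 0.9, 0.8 or 0.7, before any gain from sex and BMI category. These figures assume equal variances at the two times and a common slope, and ρ is not in the article. In the adjusted model the defect is an open specification: nothing keeps post-randomisation diet and psychological values out. Whether this would alter the treatment coefficient, by how much and in which direction cannot be determined from the article. The 0% to 32% range above only illustrates the mechanism.

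**What to change.** In Section 4.5.5:

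1. Make the between-arm analysis a linear model of the week-16 value on arm, baseline value of the outcome, sex and BMI category as used for assignment. Apply the planned multiplicity correction to the pairwise contrasts.
2. State that any further dietary, sleep or psychological covariates are baseline values only, and name them. Do not use blood glucose or lipids as dietary covariates where they are outcomes.
3. Label any model with on-trial diet, sleep, mood or adherence as a mediation or sensitivity analysis.
4. Report within-arm pre-post changes descriptively.

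The cost is analysis wording only, because sex, BMI category and baseline outcome values are already collected and diet is recalled before the start. For the psychological and sleep scales, the article should confirm that they are administered before randomisation, since it does not give their timing.

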#### 4.5.6. Ethics Concerns

The clinical trial has been registered prospectively at the ClinicalTrials.gov database (Date of approval: 13 August 2024; Identification number: NCT06553482). The protocol and all its procedures have been approved by the bioethics committee of the Medical and Psychology School at the Autonomous University of Baja California (UABC) with Code D346. At all times, interested participants must sign an informed consent form, detailing this study’s objectives, benefits, risks, and discomforts related to the protocol. Anonymity and confidentiality of the data will be ensured by assigning specific codes to individuals, and no documents will link these codes with the participant’s name or other identifying information. Additionally, this study will always obey the guidelines stipulated in the Declaration of Helsinki [24].

## 5. Expected Results

International organizations widely promote physical activity and exercise to combat non-communicable chronic diseases, which are highly associated with obesity [1]. Unfortunately, most people do not meet the minimum requirements for participation in physical activity, particularly those who are overweight or obese and who express multiple limitations in adhering to recommendations. A constant barrier is the lack of knowledge on performing specific exercises [25]. In this regard, the Physical Activity Working Group of the European Association for this study of Obesity emphasized in 2021 the need for truly functional practical exercise recommendations that focus on managing overweight and obesity. It has been agreed that a moderate-intensity aerobic exercise training program promotes substantial improvements in both weight loss and the improvement of circulating lipids, total fat accumulation, and intra-visceral fat [26].

In this context, this study will elucidate how FatMax training, both alone and in combination with resistance exercises, can enhance metabolic flexibility, increase fat oxidation, and improve body composition. This study seeks to provide critical insights into the optimization of fat utilization and the reduction of visceral fat while simultaneously preserving lean muscle mass. Additionally, expected improvements in biochemical markers—such as enhanced insulin sensitivity, improved lipid profiles, and reduced systemic inflammation—will support the formulation of targeted exercise strategies to lower the risk of chronic diseases, including cardiovascular disease and type 2 diabetes. Furthermore, anticipated epigenetic changes, particularly in microRNAs associated with adipogenesis and inflammation, will offer novel perspectives on the molecular mechanisms activated by FatMax exercise. Together, these results will lay the groundwork for evidence-based, personalized exercise recommendations that address the specific metabolic and physiological needs of this population, ultimately contributing to more effective and sustainable approaches to obesity management.

If these issues are not properly addressed, the consequences will have serious public health concerns. The prevalence of obesity will continue to rise, increasing the number of people at risk of developing chronic diseases, reducing their life expectancy, and quality of life. In addition, the health care system will face increased costs and pressure, making this silent pandemic even more difficult to manage.

As limitations of this study protocol, we cannot include a double or triple blind randomized trial, due the interventions are related to a FatMax and/or resistance training program and only the data analysis researcher will be blinded. Additionally, it is acknowledged that in addition to exercise, other lifestyle factors might influence microRNA expression, such as diet, sleep quality, emotional stress, or psychological variables, so we will include them in the correlation tests and multivariate linear regression model analysis.

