### 2.3. Interventions or Treatments

Participants will be randomly assigned to one of three groups: Group A: Will perform low-intensity training within the FatMax zone. Group B: Will perform FatMax training combined with resistance exercises. Group C (Placebo Group): The placebo group will undergo a ‘masking training’ that does not involve significant physiological or metabolic changes. This training will consist of stretching sessions with smooth, controlled movements that do not significantly impact metabolism or induce relevant physiological changes, while maintaining the perception of physical activity and an isoenergetic diet.

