### 4.2. Randomization and Blinding

The protocol involves the assignment of 52 subjects to one of three groups. Group A will comprise participants performing low-intensity training sessions within their FatMax zone. Group B will comprise participants who will perform both FatMax zone exercises as well as muscular resistance exercises (MRE). Both groups will be compared to group C, where participants will maintain their physical activity following an isoenergetic diet, evaluated through 24 h dietary records every four weeks.

For groups A and B, subjects will be allowed to perform their FatMax training on a treadmill or stationary bicycle, whichever is of their preference. The random sequence for participant assignment will be coded with SPSS 22 Software, looking for an equal distribution of both genders, BMI (overweight (≥25 and <30 kg/m^2^) and obesity grade 1 (≥30 and <35 kg/m^2^). All the evaluations and training sessions will be conducted in the Conahcyt National Laboratory of Body Composition and Energetic Metabolism (LaNCoCoME). The general process is shown in Figure 1.

To ensure single blinding, a researcher external to this study will enter data into the software on separate datasheets so that these researchers can analyze them without having access to treatment assignment information, storing all participant files in numerical order in a secure and accessible location. All files will be retained for a period of five years.

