### 4.3. Pre Intervention Exercise Test

Energy expenditure and the utilization of fat and carbohydrates at rest and during exercise will be determined by indirect calorimetry using a Metabolic Measurement System (TrueOne 2400, Parvomedics, Sandy, UT, USA), calibrated before each measurement. For basal metabolism, the subjects will remain in the Fowler anatomical position (semi-sitting supine) for continuous measurement of oxygen consumption (VO_2_) and carbon dioxide production (VCO_2_) for a period of 15 to 20 min. Subsequently, the average values of the VO_2_ and VCO_2_ recorded during a stable phase of 5 min (coefficient of variation in RQ ≤ 5%) and used to calculate energy expenditure and the macronutrient oxidation rate, using the stoichiometric equations of Weir [16] and Frayn [17], respectively.

A graded exercise protocol previously validated by the working group associated with the LaNCoCoME (Table 2) will be used to determine cardiorespiratory fitness, metabolic flexibility, and fat oxidation biomarkers. Briefly, this protocol allows an estimation of macronutrient oxidation at FatMax with a measurement error of ~1.6 g/h for carbohydrate oxidation and ~1.3 g/h for fat oxidation [18]. Distinct parameters of cardiorespiratory fitness and metabolic flexibility will also be determined by a maximal stress test exercise test on one treadmill (Quinton TM55, WA, USA) or cycle ergometer (Monark Exercise AB, Vansbro, Sweden), as described in Table 2.

Gas exchange and heart rate (Polar H10, Polar^®^ Electro OY, Kempele, Finland) will be recorded throughout the exercise tests, while the rate of perceived exertion will be registered at the end of each stage using the modified Borg scale with a 0–10 rating. The average VO_2_ and VCO_2_ values of the last 2 min of each stage before RER ≥ 1.0 will be used to calculate fat and carbohydrate oxidation using the stoichiometric equations of Jeukendrup and Wallis [19]. The maximum rate of fat oxidation and its corresponding intensity during exercise will be determined by mathematical modeling of fat oxidation kinetics, plotted against oxygen consumption (% VO_2_max) [20]. The symmetry, amplitude, and translation parameters of the curve will be calculated as well to represent the oxidative capacity of each subject.

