### 4.4. FatMax and Resistance Training: Frequency, Intensity, Time and Type

The characteristics of FatMax and resistance training are described in Table 3. In brief, the training sessions at FatMax will begin with a 5 min warm-up at 4 km/h (1°) or 50 w (60 rpm). Afterward, each patient will exercise on the treadmill or stationary bike for 40 min at their corresponding FatMax heart rate (±5 beats/min). The training volume will gradually rise up to 240 min/week, assessing gas exchange every four weeks to examine the acute metabolic response to prolonged exercise at FatMax and calculate fat utilization as recommended by Chávez-Guevara et al. [18].

In the case of resistance training, each session will have a warm-up phase of 5–10 min and a main physical conditioning phase of 30–40 min that will consist of developing a personalized circuit of strength exercises of the main muscle groups (arms, shoulders, chest, back, and legs) at moderate intensity, finishing with a cool-down of 5–10 min.

To reduce the possibility of molecular interference between FATmax training and resistance exercise, these sessions will be scheduled at least 6 to 8 h apart, ensuring adequate time for distinct physiological adaptations to each exercise modality.

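### Blinding stops at the data analyst, although nothing in the stated reason prevents coded reading of the calorimetry and exercise-test files; some secondary outcomes are left open to avoidable detection bias

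*Protocol article*

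**What the plan says.** Section 4.2 claims single blinding. The mechanism is that someone outside the study team handles data entry, using separate sheets; the stated aim is "these researchers can analyze them without having access to treatment assignment information". Section 5 repeats the limit as an acknowledged weakness: double or triple blinding is not possible with exercise programmes, and "only the data analysis researcher will be blinded".

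No section blinds the staff who run or read the tests. Section 4.2 places all evaluations and all training in the same laboratory.

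Section 2.3 calls group C a placebo group and gives it a stretching programme described as masking, "while maintaining the perception of physical activity". Section 4.2 instead describes group C as keeping up its physical activity.

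Two kinds of data differ by arm. Section 4.4 plans FatMax training with "assessing gas exchange every four weeks to examine the acute metabolic response to prolonged exercise at FatMax", which applies to groups A and B. Table 3 gives resistance sessions, which only group B does.

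**The concern.** The reason given for analyst-only blinding explains why participants and trainers know the arm. It does not explain why a person choosing a stable segment of a calorimetry trace, or reading a threshold from a panel of plots, must know it. Those readings can be made from coded files after the visit.

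An analyst's blind cannot undo a choice made when the file was read. If readers know the arm and the visit, their choices can drift towards the expected result. The resting reading matters most. It feeds resting fat oxidation and, through the rest-to-FatMax slope in Section 4.3, one of the two metabolic-flexibility indices. Fat oxidation and metabolic flexibility are both named in the hypothesis.

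The second issue is whether the analyst's blind is secure. The trial collects data that differ by arm by design, and the article withholds only the assignment itself. The third is labelling: the words placebo and masking suggest participant blinding that Section 5 rules out.

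**Working it through.** The plan states no figure for blinding, so there is none to reproduce. The check has three parts.

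**1. Which outcomes leave the reader a choice?**

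| Outcome | How it is obtained (section) | Reader latitude |
|---|---|---|
| Body composition (primary, 4.1) | DXA, impedance, air displacement (3.2, 4.5.2) | Little; instrument-read |
| Biochemistry, cytokines, microRNAs | Autoanalyser, immunoassay, PCR (4.5.1, 4.5.3) | Little; instrument-read |
| Fat oxidation during exercise, FatMax | Last 2 min of each stage before RER reaches 1.0, equations, curve model (4.3) | Limited; numerical rules |
| Resting oxidation | A 5-min stable stretch of a 15 to 20 min recording, CV of RQ at most 5% (4.3) | Some |
| Ventilatory thresholds | Algorithmic detection and also the nine-panel approach (4.3) | Some |
| Lactate threshold | Algorithmic detection among 25 approaches and also a fixed 4 mmol/L point (4.3) | Some, through choice of definition |

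For the resting window, a recording of 15 to 20 min holds 15/5 = 3 to 20/5 = 4 non-overlapping 5-min windows. If a window may start on any whole minute, there are 15 − 5 + 1 = 11 to 20 − 5 + 1 = 16 candidates. The CV rule removes some of these. How many pass is not known, and the article does not say which to take when several do.

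**2. Would attendance data reveal the arm?**

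Inputs: 16 weeks (2.6); FatMax four times a week (Table 3, where the word is misprinted) and resistance twice a week (Table 3); retention at 75% attendance (2.7 and Figure 1) or 80% (4.5.4 and Table 1). The frequencies are assumed to hold for all 16 weeks, and attendance is assumed to count both session types.

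- Group A, planned: 4 × 16 = 64.
- Group B, planned: (4 + 2) × 16 = 96.
- Group B, minimum if retained at 75%: 0.75 × 96 = 72.
- Group B, minimum if retained at 80%: 0.80 × 96 = 76.8, so 77.
- Group B attendance at which counts would overlap group A's maximum: 64/96 = 66.7%, below either retention rule.

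Among retained participants, raw counts therefore separate A from B completely. Attendance as a percentage, or as an included/excluded flag, would not. Group C's session frequency is not given, so no count can be worked out for it. Four-weekly training gas exchange would separate A and B from C, because it is described only for FatMax training. Four-weekly diet records, which Section 4.2 describes for group C, could do the same.

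**3. Does the analyst receive these fields?**

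The article does not list the contents of the datasheets or say how arms are labelled in them. The disclosure risk in part 2 is therefore conditional.

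**The case against.** **The limitation is disclosed.** That is true: Section 5 is open about it. Disclosure does not justify the part that could be avoided, and the reason offered does not reach the reading of files.

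**Most readings follow rules.** This largely stands. The resting phase has a numerical criterion, the FatMax calculation is specified, and thresholds are detected by software. What remains is the choice among qualifying resting windows, the nine-panel reading, and the choice between definitions. Automation within each method does not settle which method is reported.

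**The blinded analyst may make some of these readings.** The metabolic-flexibility indices are computed in software that is also listed for the statistical analysis. The article does not state the order of coding and reading, so this is possible. But Section 5 blinds nobody else, so any reading made by laboratory staff is unblinded.

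**Datasheet contents belong in a fuller document.** This stands. A reader might infer that the analyst's blind must fail because arm-specific data exist. The documents do not support that: the external researcher could withhold those fields and use neutral codes.

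**The placebo label is only wording.** Section 2.3 does not say that participants are blinded, and Section 5 says that they are not. The label still invites a reader to credit a blind that the trial does not have.

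**Conclusion.** The point holds in a limited form. Restricting blinding to the analyst is a stated design choice, and its stated reason does not extend to those who read calorimetry and exercise-test files. The exposure is confined to secondary outcomes with some latitude: the resting window, the nine-panel ventilatory thresholds, and the doubly defined lactate threshold.

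Two stronger readings should be resisted. First, nothing here shows that the primary body-composition comparison is compromised. Second, the bias cannot be sized from the documents. It may be tempting to set some assumed reader latitude against the fat-oxidation error of about 1.3 g/h in Section 4.3, and to compare the ratio with the design effect of 0.5. But the article gives no figure for latitude, 1.3 g/h is a measurement error rather than a between-participant SD, and the 0.5 relates to body composition.

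The analyst's blind is vulnerable: raw counts (at most 64 in A, at least 72 in retained B) or training gas-exchange data would break it if they were on the analyst's sheet. This rests on the Table 3 frequencies applying throughout. The weakness is moderate and cheap to reduce.

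**What to change.** 1. Have the existing external researcher code the baseline and week-16 test files, with arm and visit removed, before outcome readings are made. Baseline FatMax heart rate can still be read at once to set training; the outcome reading is then made from the coded file.
2. Name one lactate-threshold method and one ventilatory-threshold method in advance. It would also help to state which resting window is taken when several meet the CV criterion.
3. Have the external researcher apply the attendance rule and pass the analyst only an inclusion flag, under neutral arm codes. The 75% and 80% versions of that rule must be reconciled first. Session counts and training gas-exchange data are held back until the between-arm analysis is locked. For dietary covariates, supply the start and end recalls that Section 4.5.4 plans for all participants.
4. Describe group C as an attention control whose participants are not blinded, and reconcile its descriptions in Sections 2.3 and 4.2.

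The cost is wording and file handling by a person already in the plan. The downside is that readings are batched and come later. Coding files does not mask what happens live: perceived exertion, effort at the end of the maximal test and manual anthropometry stay unblinded, and the limitations paragraph should say so.
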